#### Statistical analysis

Prior to performing statistical analyses, detailed statistical analysis plans will be developed and published online.^39^

Our primary model development objective will seek to achieve case definition models that provide high discrimination capacity and acceptable calibration in external samples, using principled approaches to guard against overfitting biases. It is likely that there will be ambiguity in TRD determination due to a range of potential thresholds for what is considered ‘recovery‘. Consequently, sensitivity analyses may be repeated with different variations of TRD definitions. These definitions will be defined prior to analysis by expert paediatricians. We will follow a three-staged approach to identifying candidate risk factors and selecting among them. In the first stage, investigators will specify risk predictors that could be reliably and validly measured early in the hospitalisation in limited-resource settings and which are plausibly associated with TRD status. In the second stage, we will develop and validate logistic regression models, using TRD status as the dependent variable and using elastic net regression and related approaches to principled variable selection. In the third stage, we will repeat the analysis incorporating more sophisticated diagnostic assessments, such as biomarkers and ultrasound, which are available in higher resource settings. Finally, after each clinical prediction model is developed, we will use resampling methods with 10-fold cross validation to estimate model performance in terms of discriminative capacity, as measured by empirical AUROC, internally and externally.

Our secondary objective of establishing biomarker cut-offs for TRD will follow a similar receiver operating characteristic curve-based approach, except with specific biomarker concentrations as the principle predictor. A weighted evaluation of each cut-offs sensitivity and specificity will be used in a 10-fold cross-validation framework to select the optimal cut-off.^40^

The comparison of predictors, biomarkers and risk factors across the community cohort, non-TRD hospital cohort and TRD hospital cohort will be contextual and dependent on the type of variable considered. Analyses will be primarily descriptive, focused on substantive differences between cohorts, accompanied by visualisations and distribution-appropriate statistical testing.

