**Methods and analysis:**

This prospective study will enrol 662 children (aged 21 days to <18 months) seeking treatment for TDD symptoms. Children will be treated with intravenous or intramuscular thiamine (100 mg daily for a minimum of 3 days) alongside other interventions deemed appropriate. Baseline assessments, prior to thiamine administration, include a physical examination, echocardiogram and venous blood draw for the determination of thiamine biomarkers. Follow-up assessments include physical examinations (after 4, 8, 12, 24, 36, 48 and 72 hours), echocardiogram (after 24 and 48 hours) and one cranial ultrasound. During the hospital stay, maternal blood and breast-milk samples and diet, health, anthropometric and socio-demographic information will be collected for mother–child pairs. Using these data, a panel of expert paediatricians will determine TRD status for use as the dependent variable in logistic regression models. Models identifying predictors of TRD will be developed and validated for various scenarios. Clinical prediction model performance will be quantified by empirical area under the receiver operating characteristic curve, using resampling cross validation. A frequency-matched community-based cohort of mother–child pairs (n=265) will serve as comparison group for evaluation of potential risk factors for TRD.

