## Methods and analysis

### Study design and procedures

#### Study design

The study uses a prospective study design and includes a cohort of infants and young children 21 days to <18 months of age who are identified as having TDD-compatible symptoms (figure 1). Children will be recruited at the Lao Friends Hospital for Children (LFHC) in Luang Prabang, Lao PDR, and potentially eligible children presenting with any of the below described inclusion criteria will be identified through close collaboration between the LFHC hospital staff and the study team. Enrolled children will be treated with thiamine and all other clinically indicated treatments and followed closely over 48–72 hours, as described in more detail below. Based on the response to thiamine, children will either be defined as TRD cases or non-responders.

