### Case report review

To develop a clinician-guided diagnostic impression of TRD, three expert paediatricians specialised in tropical medicine will review the case reports of each hospitalised child to judge whether a child had TRD using a three-point scale (probable TRD (including classic beriberi); possible TRD and not likely TRD). Specifically, each case report will be reviewed by three expert paediatricians. When there is disagreement (defined as separate raters classifying the same case as probable TRD and not likely TRD) or when there is no agreement (ie, each rater classifies a case into a different category), efforts will be made to reach consensus between the three experts. A case report template was developed for this purpose, which includes the basic demographics of the child (sex, age), the primary concerns of the parents for taking their child to the hospital, relevant data collected during the baseline and follow-up physical examinations (4, 8, 12, 24, 36, 48, 72 hours and hospital discharge), the recovery status over the course of the hospital stay, administered treatments, findings from the echocardiogram and the cranial ultrasound, primary and secondary diagnosis by the LFHC treating physicians at the child’s discharge from hospital, dietary practices and maternal characteristics. The latter include exclusive breast feeding, maternal dietary practices with regard to a restricted postpartum diet and whether the mother experiences tingling in her fingers, an indication that the mother herself may experience clinical manifestations of severe thiamine deficiency. In addition to the case report, the expert panel will be able to review additional study data as needed.

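### Ten-fold cross-validation in a single hospital cohort gives internal performance only, so the plan cannot deliver the external AUROC it states or assess its goal of calibration in external samples

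*Protocol article*

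**What the plan says.** All statements are in the protocol article.

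- **Goal** (Statistical analysis): the primary modelling objective is models that "provide high discrimination capacity and acceptable calibration in external samples".
- **Method** (same section): after each model is built, "we will use resampling methods with 10-fold cross validation to estimate model performance in terms of discriminative capacity", and this is to be "as measured by empirical AUROC, internally and externally".
- **Abstract** (Methods and analysis): "Clinical prediction model performance will be quantified by empirical area under the receiver operating characteristic curve, using resampling cross validation". No external claim is made there, and no other performance measure is named.
- **Source of the children** (Study design): "Children will be recruited at the Lao Friends Hospital for Children (LFHC) in Luang Prabang, Lao PDR". No second hospital is named.
- **Who receives an outcome** (Case report review): "three expert paediatricians specialised in tropical medicine will review the case reports of each hospitalised child". No such review is described for community children.
- **Intended use** (Objectives of study): the case definition is to be judged for its usefulness in a range of settings.

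**The concern.** External performance means performance in children from a population other than the one that supplied the model. Cross-validation rotates which part of one cohort is held out, so every held-out child still comes from the same hospital, clinicians, referral pattern and expert panel. It corrects for overfitting but says nothing about transport to another hospital.

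If the text is followed literally, the study would report an AUROC as external when it is internal. The case definition is meant for use elsewhere, so readers would credit it with evidence that it does not have. The stated goal also has two halves, discrimination and calibration, yet the only measure fixed in the text addresses the first.

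**Working it through.** **1. The plan's own figures (Sample size).** These reproduce.

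- Non-centrality ratio: 24.386 / 12.995 = 1.877, stated as 1.88.
- Effective size: 662 / (1.88 × 1.25 × 1.25) = 662 / 2.9375 = 225.4, stated as 225.
- Power for AUROC 0.70 against 0.50 at two-sided 5% with 225 children, by normal approximation with Hanley-McNeil variance: 90.2% at 11% TRD prevalence and 94.7% at 89%. At 10% it is 87.6%, which fits the stated lower limit of 11%.

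This power concerns whether AUROC exceeds 0.5 in the population sampled. No figure in the section concerns external performance or calibration.

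**2. Is there an external sample?** The empirical AUROC is the proportion of (TRD, non-TRD) pairs that the model ranks correctly, with n1 × n0 pairs. It needs children in both outcome groups.

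| Possible external source | What the article says | TRD-labelled children |
|---|---|---|
| Another hospital | None named (Study design) | 0 |
| Community cohort | Comparison group for predictors; the community procedures list no thiamine and no follow-up of response; the expert panel reviews hospitalised children only | 0 |
| The wider multi-country project | Exchange of research results (Ethics and dissemination) | None described |

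With n1 = n0 = 0 in every row, an external AUROC is undefined, and so are an external calibration intercept and slope.

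**3. Can AUROC stand in for calibration?** No, because it depends on ranks alone. Multiply the linear predictor of a well-calibrated model by any constant c > 1: the ranking and the AUROC are unchanged, while the calibration slope becomes 1/c.

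A second illustration rests on assumptions that are not in the article: one normal predictor, logistic slope 0.75, model built at 20% prevalence, simulated.

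| Prevalence where applied | AUROC | Observed / expected events |
|---|---|---|
| 20% | 0.69 | 1.00 |
| 10% | 0.70 | 0.50 |
| 40% | 0.69 | 2.00 |

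A shift of this kind is plausible, since the Sample size section itself anticipates anything from 10% to 90% responders. Calibration measured on held-out folds of the same hospital would reveal overfitted, too extreme probabilities. It would not reveal a prevalence shift at another hospital, which only an external sample can show.

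**4. Could the study's own subgroups serve?** The eligibility change came after 0.181 × 662 = 120 children. With the plan's two 20% losses, about 120 × 0.80 × 0.80 = 77 of them would be analysable. They were enrolled under a younger age limit and a shorter list of signs, at the same hospital. Holding out that period, or one district of residence, would be imprecise and still not external.

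**The case against.** The strongest reply is that the external language is an aspiration. The objective is worded as something the team will seek to achieve while guarding against overfitting, and 'externally' may be shorthand for out-of-fold performance. On that reading the analysis is sound for a model-development study and only a word is loose. This stands in part: nothing shows the cross-validation itself to be wrong. But the label would still be wrong, and the goal would still be unassessed.

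Second, the article says that detailed analysis plans will follow. A reader might infer that the study will have no evidence on calibration, or that it fixes the wrong measure for a yes/no case definition. The document does not support either inference. Silence in an article is not a decision not to measure, and both a calibration statistic and a threshold rule can be left to the analysis plan. The primary objective is worded as distinguishing responders from non-responders, which is discrimination, and the study is powered on AUROC. Calibration is raised here only because the article makes it part of the model objective and then names a measure that cannot show it. A later analysis plan can supply the statistic, but it cannot turn folds of one hospital's cohort into an external sample.

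Third, a reader might infer that folds drawn at random will average over the November 2019 change in criteria, or that TRD cases will be few. The article does not say how folds are allocated. It anticipates 10% to 90% responders, and its secondary calculation uses TRD groups of 60 to 106. The point relies on neither inference.

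**Conclusion.** The point holds as a misstatement of what the design can estimate. There are no TRD-labelled children outside the one hospital cohort, so all cross-validated results are internal, and neither discrimination nor calibration in external samples can be assessed in this study. The sample size and the choice of AUROC for discrimination are not at fault.

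The conclusion needs no assumption about prevalence, case numbers or fold allocation. It does assume that no further TRD-labelled sample lies outside the article. Calling the estimates optimism-corrected assumes that variable selection and tuning are repeated within each fold. The size of the calibration effect (observed/expected of 0.50 or 2.00) is illustrative and rests on the assumptions stated above.

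This should be corrected: it changes what may be claimed for a case definition intended for other settings, and it costs little.

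**What to change.** 1. Delete the words 'and externally' and label every cross-validated result as internal validation.
2. State that performance in external samples is not assessed in this study and needs a separate TRD-labelled sample. Keep generalisability as an aim, not as something the study will show.
3. From the same held-out predictions, report calibration intercept and slope beside the AUROC, described as internal.
4. Optionally, add leave-one-district or leave-one-period validation as a rough look at stability. Report it as imprecise and do not call it external.

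The cost is a change of wording and a small amount of extra analysis, with no new data and no change to conduct. The downside is a narrower claim at publication.

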## Ethics and dissemination

The executive leadership of LFHC approved the conduct of the study as described here.

The presented protocol version (Version 2019-11-12) includes changes to the inclusion criteria, described in detail above. Any future modifications to the protocol including changes of study objectives, study design, inclusion criteria, sample sizes, study procedures or significant administrative aspects will be agreed on by the principal investigators and co-investigators and approved by the National Ethics Committee for Health Research, Ministry of Health (MOH), Lao PDR and the UC Davis InstitutionalReview Board (IRB) prior to implementation. The present study will be implemented among children who will be admitted to the hospital for TDD-like symptoms. Study participants will be treated by the hospital physicians following the usual hospital procedures, and the study team will not interfere with the administration of required treatments and interventions. The one study-specific intervention administered to all hospitalised study participants is thiamine. Thiamine is a water-soluble vitamin prescribed in case of beriberi or thiamine deficiency.^10 22^ Documented side effects include nausea, flushing sensation, restlessness, sweating and weakness, and there may be hypersensitivity reaction to intravenous injection or tenderness at the intramuscular injection site.^41^ All children will be examined for these symptoms over the course of the study (table 1), and any observed adverse events will be documented. Serious adverse events that are unexpected and/or probably related to the research procedures will be reported immediately to the UC Davis IRB and the National Ethics Committee for Health Research in Lao PDR.

A Data and Safety Monitoring Board (DSMB) will be established for the purpose of this project. Three independent paediatricians will monitor patient safety while the study is ongoing. Interim analyses will be completed only for safety considerations. Reports of the occurrence of potential adverse events will be submitted to and reviewed by the DSMB members. A new report will be shared with the DSMB committee each time a quarter of study participants are enrolled. The principal investigators have the right to terminate the study if the incidence of side effects and/or severity of adverse events outweigh the benefits of the study. Since thiamine administration is an established intervention with mild temporary side effects, it is expected that the study will continue until planned completion. Detailed stopping rules have not been designed at this time.

Study results will be reported following recommendations by the International Committee of Medical Journal Editors,^42^ and in accordance with the TRIPOD Statement and other relevant guidelines from the EQUATOR Network.^43 44^ The knowledge and information gained from the present study will be promptly and broadly disseminated through peer-reviewed scientific open access articles, and through communications and presentations at conferences. Moreover, the present study is part of a larger multi-country effort to address critical questions related to thiamine deficiency and public health in Asia and Africa.^45 46^ An important aspect of the overall project is to exchange research results among the collaborators. In-country result dissemination will be led by the Lao Tropical and Public Health Institute through meetings and workshops with representatives of the MOH, the Provincial Health Departments and other key stakeholders. Research briefs will also be produced for in-country distribution. In addition, the findings will be presented at the Annual Lao Pediatric Continuing Medical Education Conference organised by the Lao Pediatric Association and at the National Health Research Forum in Vientiane, Lao PDR.

## Trial status

The first participants of the hospital and community cohort were enrolled in June 2019. Changes to the enrolment criteria were implemented in November 2019 (after 18.1% of the hospital and 13.6% of the community target sample size had been enrolled). We anticipate data collection will be completed by December 2020.
